## Abstract

**Background:**

The emergence of oral delivery in cancer therapeutics is expected to result in an increased need for better coordination between all treatment stakeholders, mainly to ensure adequate treatment delivery to the patient. There is significant interest in the nurse navigation program’s potential to improve transitions of care by improving communication between treatment stakeholders and by providing personalized organizational assistance to patients. The use of health information technology is another strategy aimed at improving cancer care coordination that can be combined with the NN program to improve remote patient follow-up. However, the potential of these two strategies combined to improve oral treatment delivery is limited by a lack of rigorous evidence of actual impact.

**Methods/design:**

We are conducting a large scale randomized controlled trial designed to assess the impact of a navigation program denoted CAPRI that is based on two Nurse Navigators and a web portal ensuring coordination between community and hospital as well as between patients and navigators, versus routine delivery of oral anticancer therapy. The primary research aim is to assess the impact of the program on treatment delivery for patients with metastatic cancer, as measured by Relative Dose Intensity. The trial involves a number of other outcomes, including tumor response, survival, toxic side effects, patient quality of life and patient experience An economic evaluation adopting a societal perspective will be conducted, in order to estimate those health. care resources’ used. A parallel process evaluation will be conducted to describe implementation of the intervention.

**Discussion:**

If the CAPRI program does improve treatment delivery, the evidence on its economic impact will offer important knowledge for health decision-makers, helping develop new follow-up services for patients receiving oral chemotherapy and/or targeted therapy. The process evaluation will determine the best conditions in which such a program might be implemented.

**Trial registration:**

NCT 02828462. Registered 29 June 2016.

## Background

Oral delivery in cancer therapeutics is an emerging issue within the general context of health care cost control and patients’ desire to receive high-quality care at home [1]. This new practice generates needs for better coordination between the treatment stakeholders (patients and care providers) along the care continuum [2–6]. Indeed, in comparison with parenteral chemotherapy (which requires professionals to deliver medication themselves) the use of oral agents allows remote follow-up. Yet, given the toxicity of the medication and its potential side effects, both patients and professionals in the community need to be provided with enhanced information in order to ensure adequate treatment delivery and maximal efficacy. Indeed, high rates of non-adherence to oral anticancer drugs (often associated with a poor Relative Dose Intensity) have been reported in the literature [6, 7], implying adverse impacts on the efficacy and toxicity of the medication - along with an increased use of health care services [8–10].

In line with this need for improved coordination, navigation programs are becoming a major trend in oncology [11, 12]. Their aim is to address the widespread problem of access to (and continuity of) care [13], and these programs often rely on Nurse Navigators who are in charge of improving transitions of care by providing information about cancer (from prevention to treatment), assisting patients with medical paperwork, facilitating patient-provider communication, scheduling appointments, addressing transportation issues and mobilizing patient financial resources [14, 15]. These navigation programs are based on health information technology that has already demonstrated positive impacts on patient self-management with regard to pain and disease symptoms [16–18], as well as patient adherence to oral therapies [19, 20]. However, evidence on the impact of such navigation programs remains scarce. Some programs have proved successful with positive outcomes identified - such as improved patient care, better access to screening tests, and better cancer follow-up rates and timeliness [11, 21–24]. Regarding their economic impact, few economic evaluations of such programs have been conducted for patients having cancer, though not specifically receiving oral therapeutics - with nuanced results on their cost-effectiveness, depending on the perspective adopted for the evaluation [25, 26]. Overall, few studies have provided evidence regarding the impact on quality of care.

Further evaluations relying on randomized controlled trials are therefore needed to provide rigorous evaluation of these programs [27]. The study of the CAPRI program, developed within the Gustave Roussy Comprehensive Cancer Center, aims to address this specific issue. This trial first seeks to measure the impact of a new navigation system combining Health Information Technology (via a web portal) and Nurse Navigators (NN) [28] on treatment delivery for patients with metastatic cancers who are receiving oral chemotherapy and/or targeted therapy. Improved treatment delivery is expected for patients benefiting from the CAPRI program, since this last is supposed to strengthen links between hospital professionals, primary care physicians, pharmacists and nurses in the community.

This paper details the study protocol of a Randomized Controlled Trial (RCT) evaluating the efficacy of a new navigation program named CAPRI. The primary objective is to examine whether it leads to better treatment delivery among metastatic cancer patients treated with oral chemotherapy and/or targeted therapy, in comparison with those receiving only usual care. A secondary objective is to examine how the CAPRI program influences several aspects associated with patient care including tumor response, survival, toxic side effects, quality of life and patient experience. The study also includes both an economic evaluation and a parallel process evaluation.

## Method/design

### Study setting

The proposed Randomized Controlled Trial is a large-scale trial designed to assess the impact of an innovative navigation program denoted CAPRI, that is based on two Nurse Navigators and a web portal and ensures coordination between community and hospital as well as between patients and navigators, within the context of routine delivery of oral anticancer therapies. The broad research aim is to assess (a) the program’s impact on oral therapeutic delivery for patients with metastatic cancer treated with oral chemotherapy and/or targeted therapy, and (b) CAPRI’s effectiveness in terms of the treatment’s toxic side effects, tumor response, Progression Free Survival, Overall Survival, patient quality of life and patient experience, and (c) the economic evaluation of the CAPRI program.

The study will evaluate the CAPRI’s efficacy in comparison with usual care. The RCT will randomize 1,000 individuals fulfilling inclusion criteria into either the CAPRI group or the control group, for a 6-month period (Fig. 1). Participant outcomes could be assessed at baseline (T0) and each month of intervention, excepted for quality of life (T1 – T6) and patient experience (T6). Control group participants will be offered the intervention when the CAPRI program ends for the intervention group.

**Fig. 1 Fig1:**
[figure not shown]
Flow Chart of participant’s progress through the different phases of the study

### Participants

Recruitment will take place at the Gustave Roussy Comprehensive Cancer Center and will be open to patients with metastatic cancer taking oral chemotherapy and/or targeted therapy. 1,000 patients initiating oral therapeutics will be recruited. Recruitment will be managed by the referring department at Gustave Roussy.

### Eligibility criteria

All participants will be required to speak French and be aged 18 years and older. To be included in the study, they will have to have a performance status, corresponding to the OMS score, of between 0 and 2, and their life expectancy must be of at least 6 months. They must consent to follow-up assessments. Exclusion criteria include being under hormonotherapy only, not having a referring general practitioner (GP), having neither internet nor phone access, and being deprived of liberty.

### Sample size calculation

Given previous research showing Relative Dose Intensity (RDI) varying from 60% to 95% for oral therapeutics in cancer care, considering a Relative Dose Intensity lower than 85% as a signal for reduced survivorship, and considering that a difference of 6% to 20% was found between different treatment options or between different cancer types, we expect a sizeable effect of the CAPRI program on patient RDI (5% difference with the control group) [29–32]. Therefore, 393 individuals per group will be sufficient to detect a difference in RDI between the CAPRI program and usual care, assuming significance is set at 5% (α = 0.05) power at 80% and a standard deviation of 25% for the distribution of mean change. We will include an additional 27% (*N* = 107 per group) to allow for attrition.

### Participant recruitment procedure

Depending on their cancer stage and treatment option, participants will be invited to join the cohort by their referring committee at Gustave Roussy, which will be responsible for their eligibility. In Gustave Roussy, each of these departments is composed of medical doctors, specialized in a specific type of cancer. Those patients considered eligible will be directly offered the CAPRI program by their oncologist, and provided with the participant information pack. Then, the referring oncologist will provide each patient with a consent form, if they are interested. Baseline measurement collection will be conducted only for consenting participants, following randomization. Patients in the intervention group will then meet the Nurse Navigators for an initial appointment, at which they will be given a starter box detailing login details, as well as a guide to using the portal.

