### Randomization procedure

In accordance with CONSORT guidelines [33, 34], randomization will occur once participants have completed their consent form. Given the potential difference in adherence and socioeconomic status among the different cancer types [35, 36], stratified randomization might be used in order to minimize these differences between and within groups. This randomization will be done via computer software and completed by an independent researcher (Gustave Roussy randomization department). A randomization number will be allocated to each participant, and results of the randomization will be sent to both the therapist and the nurse navigators. Participants included in the intervention arm will be given immediate access to the CAPRI program, including access to their personalized online portal.

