#### Secondary endpoints

Secondary endpoints will be patient adherence to oral anticancer therapy, quality of life (functional scales, symptom scales, global health status and quality-of-life scales), patient experience, tumor response, Progression Free Survival (PFS), Overall Survival (OS) and toxic side effects of the therapy (severity and quantity). We expect that patients in the intervention arm, by comparison with controls, will demonstrate significantly greater improvements in secondary outcomes measures. Demographic, socio-economic and clinical variables will be assessed and considered in order to adjust the study results. These adjustment factors could be used to make stratified group comparisons.

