#### Instruments of measurement

Outcomes will be assessed by a Clinical Research Associate (ARC) at baseline, and each month until the end of the program (after 6 months), excepted for patient quality of life (at baseline, after 3 months and at the end of the program) and for patient experience (at the end of the program). Instruments used to collect data from participants, including primary and secondary outcomes, are listed in Table 2.

**Table 2 Tab2:** Variables and Instruments used for data collection

Measurement tools ARC administered (face to face interview)		Time point			
		At baseline	Each month	After 3 month	After 6 months
Demographics and general medical history	Age, gender, comorbidities	*			
Socioeconomic status	Education, income, employment, family characteristics	*			
Diagnosis	Cancer type, stage	*			
Autonomy	OMS score [55]	*	*	*	*
Treatment Delivery	RDI ratio [30] Morisky questionnaire [56] MEMs (only for targeted therapy) [57]		*	*	
Toxic effects	NCI-CTC-AE (CTCAE v4.0)		*	*	
Overall Survival	OS		*		
Progression Free Survival	PFS		*		
Tumor response	RECIST [58]		*		
Quality of life	EORT QLQ-C30 [59]	*		*	
Patient experience Satisfaction	PACIC [60]				*

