### Data analysis

Appropriate descriptive statistics will allow presentation and comparison of sample characteristics at baseline, and at each evaluation time point. The primary analyses will utilize a between-group design (CAPRI versus control groups) at six time points (each month)). Significant change in treatment delivery will be measured on the RDI ratio, calculated with the Morisky score and/or the Medication Event Monitoring System (MEMs) results. If distribution is normal, a student *t*-test will be used to compare RDI means, as well as secondary outcomes designed as continuous variables. If not, a Mann–Whitney test will be used. Chi2 or Fisher’s test will be used to compare secondary outcomes designed as binary variables. Baseline data will be examined to analyze probability of attrition bias.

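### Baseline is collected after randomization with no described masking, so self-reported baseline items, chiefly the QLQ-C30, may reflect knowledge of the allocation

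*Protocol article*

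**What the plan says.** The Protocol article fixes the order of steps in two sections that agree with each other. Under Randomization procedure, "randomization will occur once participants have completed their consent form". Under Participant recruitment procedure, "Baseline measurement collection will be conducted only for consenting participants, following randomization". The latter section then adds: "Patients in the intervention group will then meet the Nurse Navigators for an initial appointment". The order is therefore consent, randomization, baseline, navigator appointment.

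On who knows the allocation, Randomization procedure says that "results of the randomization will be sent to both the therapist and the nurse navigators", and that "Participants included in the intervention arm will be given immediate access to the CAPRI program". No section describes masking of patients, clinicians or the research associate who assesses outcomes.

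On what is measured, Table 2 (Instruments of measurement) lists the QLQ-C30, the OMS performance score, and demographic, socio-economic and diagnostic items at baseline, under a heading of face-to-face interview. The text of that section gives monthly assessment, "excepted for patient quality of life (at baseline, after 3 months and at the end of the program").

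On how baseline is used:
- Secondary endpoints expects that intervention patients "will demonstrate significantly greater improvements in secondary outcomes measures".
- The same section plans adjustment for demographic, socio-economic and clinical variables.
- Data analysis states: "Baseline data will be examined to analyze probability of attrition bias".

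**The concern.** A baseline value is a safe reference or covariate only if the allocation cannot have influenced it. Here the oncologist has already offered the patient the program, the patient has consented, and the computer has assigned a group before the quality-of-life questionnaire is given. A program of phone calls and a personal portal cannot be hidden from the people who receive it. A patient who knows the result may answer subjective items differently, and the interviewer may record them differently.

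Two things are at stake. First, if baseline quality of life is shifted in one arm, an analysis of change carries that shift into the treatment effect, and an analysis adjusted for baseline carries part of it. Second, a patient who leaves between randomization and baseline supplies no interview data, so the attrition check cannot describe that patient.

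**Working it through.** **1. Order and disclosure.** The two procedural sections agree, so the order is not a slip in one sentence. They differ on how soon the program starts. Randomization procedure gives intervention patients access at once. Participant recruitment procedure puts the navigator appointment, where login details are handed over, after baseline. On the second reading, baseline precedes exposure to the program, and only knowledge of the allocation is at issue. Neither section says when patients or the research associate learn the group, and neither requires baseline to be completed first.

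**2. Which items are exposed.**
- QLQ-C30: self-reported and subjective, so exposed.
- Self-reported socio-economic items: possibly exposed.
- OMS score: largely protected, because Eligibility criteria require a score of 0 to 2 and it must be known before entry.
- Age, gender, cancer type and stage: fixed facts, not exposed.

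Study setting gives quality of life at T1 to T6, with baseline called T0. Instruments of measurement and Table 2 both schedule a baseline value. These need reconciling, and the quality-of-life part of this point rests on the latter two.

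**3. Which analyses are exposed.** Table 2 gives Relative Dose Intensity (RDI) no baseline entry, and Data analysis compares RDI means between groups. The primary comparison therefore does not use baseline. The same section names a t-test or Mann–Whitney test for continuous secondary outcomes, and names neither a change score nor a baseline quality-of-life covariate. The link to baseline comes from the improvement wording and the adjustment plan in Secondary endpoints.

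**4. The plan's own figure, as background.** With a difference of 5, SD 25, two-sided α 0.05 and power 80%:

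n = 2 × (1.960 + 0.842)² × 25² / 5² = 2 × 7.85 × 25 ≈ 392.5, rounded up to 393 per group.

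This matches Sample size calculation. The point does not depend on it; 393 is only the group size used next.

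**5. Illustration of size (assumptions, not in the documents).** Assume no true effect, SD 1 at both times, correlation ρ between baseline and follow-up, and a shift b (in SD) in one arm at baseline only.

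- Change score: bias b, SE = √(2(1−ρ)) × √(2/393)
- Baseline-adjusted (ANCOVA): bias ρb, SE = √(1−ρ²) × √(2/393)
- Rejection = 1 − Φ(1.96 − bias/SE) + Φ(−1.96 − bias/SE)

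For b = 0.1 and ρ = 0.5, √(2/393) = 0.0713. The change-score ratio is 0.1/0.0713 = 1.40, giving 0.289. The ANCOVA ratio is 0.05/0.0618 = 0.81, giving 0.128.

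| b | ρ | Change score | ANCOVA bias | ANCOVA rejection |
|---|---|---|---|---|
| 0.1 | 0.3 | 22% | 0.03 | 7% |
| 0.1 | 0.5 | 29% | 0.05 | 13% |
| 0.1 | 0.7 | 44% | 0.07 | 28% |
| 0.2 | 0.3 | 66% | 0.06 | 14% |
| 0.2 | 0.5 | 80% | 0.10 | 37% |
| 0.2 | 0.7 | 95% | 0.14 | 79% |

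A comparison of follow-up means that leaves baseline out has no such bias and stays at 5%.

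**6. Direction.** If controls score lower at baseline from disappointment and there is no true effect, controls show the larger improvement, so false rejections favour control. If intervention patients answer more positively at baseline, the result is the same. The opposite reactions would favour CAPRI. Nothing in the documents says which occurs.

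**7. Attrition check.** The plan allows 107 extra per group (393 + 107 = 500; 107/500 = 21.4%). It does not say how much of that loss would fall before baseline. Each participant receives a randomization number, so early losses can be counted by arm. The interview data of those patients are what would be missing.

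**The case against.** The strongest reply is that the text does not show that any baseline value is distorted. Results are sent to the therapist and navigators, and when patients are told is not stated. The navigator appointment follows baseline. Controls are not refused the program: Study setting offers it to them when the program ends for the intervention group, which weakens the idea of disappointed controls. The named tests use no baseline quality-of-life value, most adjustment variables cannot move with knowledge of allocation, and the shifts in the illustration are assumed. A shift that persisted unchanged to follow-up would also cancel in a change score.

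All of this stands, and it limits the point. A reader might infer that baseline is certainly contaminated, that every adjusted comparison is biased, that CAPRI is favoured, or that the primary result is in doubt. The documents support none of these: disclosure timing is not stated, the adjusters are mostly fixed facts, the direction is open, and RDI has no baseline.

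What the reply does not remove is the fixed order itself. Baseline follows randomization, no masking is described, and nothing holds back the allocation until the questionnaire is done.

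**Conclusion.** The point holds in limited form, as a should-fix. Self-reported baseline items, chiefly the QLQ-C30, may be influenced by knowledge of the allocation, and patients lost before baseline would be absent from the baseline data used to examine attrition. This affects change or baseline-adjusted analyses of quality of life, adjustment for self-reported items, and the attrition check. It leaves the primary RDI comparison and unadjusted comparisons of follow-up means untouched.

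The documents give no basis for estimating the size or direction of the bias. The illustrated rejection rates show only that a modest shift would matter if a change score or ANCOVA were used; they are not a prediction. The conclusion assumes that patients can learn their group before answering, which the text permits but does not state.

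**What to change.** Amend Participant recruitment procedure and Randomization procedure so that the Table 2 baseline items, at least the QLQ-C30 and the other self-reported items, are completed after consent and before the allocation is generated or released. Make a completed baseline form a condition for randomization. Randomization already runs through computer software and an independent department, so this is a reordering of existing steps. The cost is a few forms from patients who are not then randomized. The documents do not say whether consent, randomization and baseline share one visit, so the practical burden should be checked locally.

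Recruitment began in October 2016, and reordering cannot repair baselines already taken. For those patients:
- record whether baseline was completed before or after the allocation was disclosed;
- report losses between randomization and baseline by arm;
- add a sensitivity analysis of follow-up quality of life without the baseline score.

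The quality-of-life schedules in Study setting and Instruments of measurement should be reconciled in the same amendment.

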### Randomization procedure

In accordance with CONSORT guidelines [33, 34], randomization will occur once participants have completed their consent form. Given the potential difference in adherence and socioeconomic status among the different cancer types [35, 36], stratified randomization might be used in order to minimize these differences between and within groups. This randomization will be done via computer software and completed by an independent researcher (Gustave Roussy randomization department). A randomization number will be allocated to each participant, and results of the randomization will be sent to both the therapist and the nurse navigators. Participants included in the intervention arm will be given immediate access to the CAPRI program, including access to their personalized online portal.

